## INTRODUCTION

Cardiovascular diseases (CVD) include coronary heart disease, cerebrovascular disease, congenital heart disease, deep vein thrombosis, pulmonary embolism, and disorders affecting the heart and blood vessels. (1). A number of risk factors are often associated with acute CVD (1,2) and, at the socio-demographic level, poorer economic or educational conditions may contribute to increased risk factors (3). CVD accounts for 31% of deaths and is the leading cause of mortality worldwide (1,4). (1,4). Coronary heart disease alone accounts for 19% of global deaths in men and 20% in women (1). (1). In Spain, according to the Instituto Nacional de Estadística, CVD caused 24% of all deaths in 2020 (5).

Major surgery is often chosen as the treatment of choice for CVD, with patients often classified as "high risk" due to comorbidities such as frailty, obesity or advanced age. (6). These patient characteristics may increase the likelihood of postoperative pulmonary complications such as pneumothorax, atelectasis, pneumonia, need for prolonged mechanical ventilation, pulmonary oedema or respiratory distress syndrome (7,8).

The concept of *fast-track* rehabilitation after surgery (ERAS, Enhanced recovery after surgery) appeared in the 1970s, and combines different measures to optimise the patient's condition before, during and after surgery in order to allow them to recover their maximum functional capacities as quickly as possible after the surgical procedure. (9-12). Although this concept was initially introduced by surgeons, it is now a transdisciplinary approach that can only be successful with the synergistic involvement of the entire healthcare team. The ERAS (Enhanced Recovery After Surgery) protocol represents a model of patient-centred healthcare collaboration (9,11,13). Despite the name of the protocol, rehabilitation places great emphasis on both preoperative preparation and postoperative re-education (9-13). Furthermore, at a time when controlling health care costs is an ever-present concern, participation in these exercise-based prehabilitation programmes (EBPrehab) may decrease postoperative complications and length of hospital stay (LOS) (9,11,12). (9) improving patients' functional capacity and decreasing healthcare costs (14).

## **METHODOLOGY**

### Design

A prospective, parallel, non-randomised, single-centre, prospective clinical trial protocol has been designed. In this study, participants will be randomly assigned to either the experimental prehabilitation group or the conventional prehabilitation group during the three weeks prior to surgery.

This study complies with the ethical principles established in the Declaration of Helsinki and is made available to the Ethics Committee of the Hospital de La Ribera. If approved, it will be registered in the U.S. National Library of Medicine (ClinicalTrials.gov).

All candidates will be given and explained an information sheet (Annex I) with detailed information on the study and will be asked for their express consent and signature, after reading and explanation, as a requirement for participation in the study.

### Participants: eligibility and recruitment.

Ninety-six patients will participate in this study, whose recruitment is expected to take place between June 2023 and July 2025. The inclusion criteria for the sample will be: adult patients diagnosed with valvular pathology who have been admitted as candidates for cardiac surgery for the first time, and whose appointment for intervention has been scheduled. Only those who voluntarily agree to participate in the study and sign the informed consent form will be admitted. Patients with the following characteristics will be excluded: stage 4 or 5 renal failure, low ejection fraction, Euroscore greater than 15, non-ST-segment elevation acute coronary syndrome (NSTEMI) and coronary artery disease or need for urgent intervention.

Those with cognitive deficit, diagnosis of pulmonary disease, heart failure, unstable angina, arrhythmias, severe aortic stenosis, mitral regurgitation, aortic aneurysm, recent embolism, recent myocarditis or pericarditis, or comorbidities limiting the performance of the functional test will also be excluded.

All persons referred to the Physiotherapy Unit from the Cardiac Surgery Unit of the Hospital de La Ribera (Alzira, Spain) will be considered candidates for this study, as long as they attend the initial physiotherapy assessment. Recruitment will therefore be carried out among these attendees and eligibility will be confirmed by a physiotherapist. Signed informed consent will be collected prior to any measurement or intervention.

The assignment of each participant to one group or another is not the responsibility of the researchers, but will be randomised. The initial and final evaluation will be carried out by three physiotherapists who will act without knowing the assignment of each participant to one or the other group. The physiotherapists who carry out the measurements will attend a training session to unify the measurement criteria for each variable.

### Intervention

Figure 1 shows how the intervention and measurement protocol will be developed in each of the groups. Both groups will receive a first session in which they will be instructed to carry out the unsupervised home EBPrehab programme, consisting of respiratory training, ventilatory work and strengthening of the respiratory muscles, aerobic endurance exercise through continuous walking, and a series of measures on post-surgical care. Once the guidelines have been explained, they will be given a series of links to explanatory videos so that they can carry out the work at home seven times a week without supervision. For this intensity adjustment, individual perception of exertion will be used, using a Borg CR-10 scale (29). Participants will be instructed to maintain a moderate intensity, between four and seven on this scale. Aerobic endurance exercises shall be performed in a continuous and harmonious rhythm.

Figure 1. Flow chart. .

[figure not shown]

In addition, a preoperative musculoskeletal and cardiopulmonary rehabilitation programme will be implemented in the experimental group for the cardiovascular patient who underwent surgery for valvular heart disease. The intervention has been designed following the guidelines of the American College of Sports Medicine (ACSM) for exercise prescription, considering the FITT-VP principles (Frequency, Intensity, Type, Time, Volume, Progression) for patients with cardiorespiratory pathology and adjusting them to the surgical population. (28). This peripheral muscle strengthening programme (Figure 2) will be modified and adapted in each classroom session, which will require a weekly evaluation and modifications in terms of the load and the number of series and/or repetitions, depending on each participant (29). For this work, participants will also be educated to adjust the intensity using the Borg scale CR-10 (29) by asking them to maintain a moderate intensity, between four and seven on this scale.

Figure 2. Common and group-specific interventions....

[figure not shown]

The pre-rehabilitation will be structured in three different phases (Supplementary Material 1):

1. Breathing training phase (Conventional treatment group and experimental group, 20 min). The breathing intervention will include diaphragmatic breathing (3 sets of 10 repetitions), chest expansion exercises (3 sets of 10 repetitions) and incentive spirometry with the Portex® Coach 2® Incentive Spirometer 4000 ml (1 set, with 10 repetitions up to 25% of maximum capacity, and only 1 repetition at maximum inspiratory capacity). Expiratory flow techniques will be taught, using the Sibelmed® DatoSpir Peak-10 incentive device, and finally, specific training of the respiratory muscles will be carried out using the Threshold® Inspiratory Muscle Trainer

(Respironics, NJ 07054, USA), adjusting the workload to a minimum of 30% of the subject's PIM. (16,30). The workload range of the IMT device will be 9 to 41 cmH2O. The protocol will contain 20 min of training divided into seven sets, with two minutes of work and one minute of rest between sets. Each participant will receive a list of links to demonstration videos and instructions on how to perform each of the exercises.

2. Aerobic endurance training phase (Conventional treatment group and experimental group), 10 min, increasing by five minutes at each training session, up to 20 min. Each patient will walk in a continuous harmonic mode, following the minimum recommendations of the World Health Organisation. (31). Perception of exertion will be assessed using a modified Borg scale.
3. Peripheral resistance training phase (for the experimental group only). 10 min, increasing by five minutes at each training session, up to 20 min. In each session, participants will complete three sets of four exercises. During the first sessions, training will consist of 8 repetitions of the exercises, performed with light resistance bands, and emphasising analytical training of the main muscles (deltoids, biceps brachii, triceps brachii, abdominals, trunk extensors, quadriceps, hamstrings and calves). (32). After the second training session in the hospital, progress to using medium resistance bands and/or increasing repetitions for each exercise. In the final phase, the volume will be increased to 12 repetitions. Each exercise will be rested for 60 seconds.

To verify that participants perform the exercises at home, regardless of the group to which they are assigned, they will be asked to record their activities at home using the Google Fit application. (33).

The prehabilitation programme common to all participants is the same programme that is conventionally carried out in the prehabilitation service of the Hospital La Ribera. In that sense, although there is no evidence that the exercises proposed before surgery can cause harm to cardiac patients awaiting surgery, to minimise the risks the first session will be carried out in the hospital, adapting the intensity to each individual. Any adverse situation perceived by the patient during the home sessions will be reported. All adverse effects will be evaluated, recorded and discussed in the final article.

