  - **Respiratory pressures:** These are used to calculate the strength of the respiratory muscles, both at the diaphragmatic (inspiratory) and abdominal and intercostal (expiratory) levels. Maximum static inspiratory pressures (MIP) and maximum static expiratory pressures (MEP) will be measured in a seated position, using a MicroRPM device (Carefusion, VYAIR MEDICAL, UK). A careful explanation of the test will be given, encouraging the patient to perform a maximal inspiration and inspiration of approximately 2-3 seconds against the resisted device. Predicted values will be estimated using the equation proposed by Heinzmann et al.(40).
4. Exercise capacity. Exercise capacity and endurance will be collected before, 24 hours after surgery and at discharge. The tests used will be:
- **Aerobic capacity:** will be assessed by the 2-minutes Step Test, a valid tool to assess functionality in patients with cardiac pathology after surgery and sensitive to assess perioperative changes. (41)which also has excellent inter-examiner reliability (41). (41). Following the protocol established by Jones and Rikli (42)implemented in 2022 by Chow et al. in revascularised individuals (41)the aim of this test is to count the number of repetitions that each participant is able to perform in two minutes. In case a person needs technical assistance to perform the test, a stable chair will be placed close to him/her to limit the risk of falling. The assessor shall use a manual counter to record the number of steps each person takes by lifting one knee to the middle distance between the patella and the anterior superior iliac spine. (42).
  - **Manual grip strength:** grip strength capacity shall be recorded with manual dynamometry (kg), using a Jamar Plus+® device, which is reliable for measuring changes in patients with cardiac disease, and whose minimum detectable change is 5.2 kg and 5.1 kg for the right and left hand, respectively. (43). With the patient in a seated position, a maximum hand closure is requested for 2-3 seconds, the hand is changed, and the operation is repeated up to 3 times, with a difference of less than 10% between measurements. This tool has inter-examiner reliability (44).

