#### Data collection

Sex, age, underlying pathology, comorbidities, body mass index (BMI) and toxic habits will be the descriptive variables collected in both groups. All these data will be stored in their clinical history and will be extracted by the person in charge of epidemiological data management at the hospital, who will include them in an Excel table, also indicating whether each participant survives or not, as well as the information related to the intervention and the pathology, catalogued using the International Classification of Diseases 11 (ICD-11) or the appropriate one if there are updates. Days of hospitalisation, intensive care unit (ICU) stay, if applicable, Charlson comorbidity index, and possible postoperative complications for each participant will also be reflected in this table.

Although the database from which the data will be extracted will not contain personal data, as each participant will receive a numerical identification code, all researchers will sign a data confidentiality commitment sheet prior to the start of the study, which states that patients' personal data will be protected.

The medical information of each participant and his or her evolution at each point of the measurement shall be recorded in his or her medical record.

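### The protocol promises to record all adverse effects, but its only described preoperative route is what patients notice in home sessions, and staff contact may differ by arm

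*Protocol*

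**What the plan says.** The Design section places both programmes "during the three weeks prior to surgery". The Intervention section gives the experimental group an extra component: "Peripheral resistance training phase (for the experimental group only). 10 min, increasing by five minutes at each training session, up to 20 min".

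On safety, the last paragraph of the Intervention section has two consecutive sentences. The first is "Any adverse situation perceived by the patient during the home sessions will be reported". The second is "All adverse effects will be evaluated, recorded and discussed in the final article". The same paragraph places the first session in hospital as a precaution, for both groups.

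Data collection describes what the hospital's data manager extracts into the analysis table. This includes survival ("also indicating whether each participant survives or not"), hospital and ICU days, the Charlson index, and complications after surgery ("possible postoperative complications for each participant will also be reflected in this table"). That section also says: "The medical information of each participant and his or her evolution at each point of the measurement shall be recorded". That entry goes into the medical record.

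On contact with staff, the Intervention section describes the resistance programme as adapted at each classroom session with a weekly evaluation, and ties progression to a second hospital training session. No such repeated contact is described for the conventional group.

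**The concern.** A promise to record everything delivers only what some source brings to light. For the three weeks in which the tested component is given, the one described source is passive (nobody asks), depends on the patient noticing something, and is tied to home sessions. The extraction that could catch the rest lists no event before surgery.

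Two things are at stake. The first is completeness. The Introduction says that, to the authors' knowledge, no published cardiac prehabilitation programme has included resistance training, and the protocol commits to discussing adverse effects in the article. All three hospital-stay variables start at or after the end of surgery. A patient who dies or deteriorates beforehand, and is not operated on, therefore has no primary outcome, and the table would hold at most an undated survival status.

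The second is comparability. If staff see experimental patients every week and control patients only at the first session, the same background symptoms of valve disease can be recorded more often in one arm. The safety comparison would then partly reflect who was asked.

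**Working it through.** **1. The plan's own figure.** The protocol states no harm rate or expected event count. Its one computed design figure is the sample size, and it reproduces. With effect size 0.613, two-sided alpha 0.05 and power 0.80, a two-sample t-test needs 42.76, so 43 per group. Then 43 / (1 − 0.10) = 47.8, so 48 per group and 96 in total. The present point does not depend on this.

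**2. Routes, by kind of event.**

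- *Noticed by the patient in a home session:* covered, passively, in both arms.
- *In a hospital training session:* staff are present, and the general promise applies, but no recording route or table field is named.
- *Between sessions or delayed:* no route named.
- *Admission, cancelled surgery or surgery made urgent before the planned date:* no field in the extraction list.
- *Death before surgery:* survival is extracted, but without date or phase.
- *After surgery:* complications are extracted.

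**3. Is the session-based window equal between arms?** Inputs from the Intervention section: home work seven times a week for three weeks, so 7 × 3 = 21 sessions; breathing 20 min; walking 10 min rising by 5 to 20 min; resistance training with the same durations as walking. The home frequency of resistance training is not stated, so both readings are shown.

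- *Resistance training only in hospital or classroom sessions:* home minutes are the same in both arms, ratio 1.0.
- *Also daily at home, duration rising each session:* breathing 21 × 20 = 420; walking 10 + 15 + 19 × 20 = 405; control 420 + 405 = 825; experimental 825 + 405 = 1230; ratio 1230 / 825 = 1.49.
- *Also daily at home, duration rising weekly:* walking 7 × (10 + 15 + 20) = 315; control 420 + 315 = 735; experimental 735 + 315 = 1050; ratio 1050 / 735 = 1.43.

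The list of home activities in the Intervention section does not include resistance training, so 1.0 is a live possibility.

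**4. Share of training sessions under the home rule.** With one hospital session in the conventional group, 21 / 22 = 95%. If the experimental group has 2 to 6 hospital sessions in addition to the 21 (an assumption; the number is not stated), the share is 21 / 23 = 91% down to 21 / 27 = 78%. Most training sessions thus have a described route. The gap is in hospital sessions and the time between sessions.

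**5. What unequal contact could do (illustration, assumed rates).** Suppose the true risk is 10% in both arms of 48, so 4.8 events each. If 50% are detected in controls and 60% to 100% in the experimental arm, the recorded counts are 2.4 against 2.9 to 4.8, an apparent ratio of 1.2 to 2.0. With 80% against 90%, the ratio is 1.1. None of these detection rates comes from the protocol.

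**The case against.** The strongest reply is that the home-session sentence is not an exclusive rule. It reads naturally as a supplement for the setting where staff cannot observe, and the sentence after it covers all adverse effects without limit of place or time. The patient's evolution is also entered in the medical record at each measurement point, including the pre-surgery one. This stands in part: it would be wrong to say that the protocol restricts adverse events to home sessions, or that extraction is confined to postoperative complications, since survival is extracted too. But a general promise does not say how an event between sessions becomes known, and a medical-record entry reaches the analysis only if the extraction list calls for it.

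A reader might infer that most harms go uncounted because exercise minutes are a small part of three weeks. The documents do not support that. Minutes are not harms, no event or detection rate is given, and the home rule covers most training sessions.

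A reader might also infer that the capture window is longer in the experimental arm. That needs daily resistance training at home, which the text does not state. The three weeks and the home rule are the same for both groups.

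Nor do the effortful tests at 24 hours and discharge clearly go unmonitored. The protocol foresees a fall risk in the step test ("a stable chair will be placed close to him/her to limit the risk of falling"), but those two assessments are done by staff on inpatients, in the period for which complications are extracted.

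The 10% dropout allowance (0.10 × 48 = 4.8 per arm) is a sample-size assumption, not a rule for classifying events, and it does not show that deteriorations would be hidden there.

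Finally, the flow chart and the figure of group-specific interventions are not available here and may show a visit schedule for the conventional group. Tabulation of events may sit in an analysis plan. How events are collected, however, is protocol content, and an analysis plan can only tabulate what was collected.

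**Conclusion.** The point holds in this form. The protocol promises complete recording of adverse effects but, for the preoperative period, describes only a passive route tied to home sessions, and its extraction list has no preoperative event field. Events between sessions, in hospital training sessions, or leading to a changed surgical course have no stated path into the analysis table. The asymmetry that the text itself supports is the weekly face-to-face evaluation described for the experimental arm alone, subject to what the missing figures show.

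The size and direction of any bias cannot be computed. Home-session time differs by a factor between 1.0 and about 1.5, depending on an unstated home frequency, and the effect of unequal contact depends on detection rates the protocol does not give. It is worth changing because the safety comparison depends on it and the cost is low. It does not affect the sample size.

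**What to change.** In the safety paragraph of the Intervention section, state one rule for both arms: adverse events are collected from assignment to discharge, whenever they occur, including hospital sessions, study tests and the time between sessions. Use the same short solicited symptom question in both arms on the same schedule, attached to the home activity record that both groups are already asked to keep. The three blinded physiotherapists should not ask it, because answers about exercise symptoms could reveal the resistance work. Tying it to the home record also avoids relying on the pre-surgery measurement, whose timing relative to training is not stated.

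In Data collection, start the extraction at assignment and add fields for preoperative admission, cancelled or urgent surgery, and date of death. Report these by arm for all assigned patients, separately from dropout.

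The cost is protocol wording, one question on an existing record and a few extra fields in an extraction already planned. The downside is slightly more patient and data-entry time, and a higher reported event count, which the report should attribute to active questioning.

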### Variables

The variables will be divided into four different areas, differentiating between hospital stay, quality of life, respiratory values and exercise capacity (Figure 3).

Figure 1. Variables, tools and timing.

|          | Hospital stay.                                                                                                                                                                                | Quality of life.                                              | Respiratory values.                                                                                                                                                                                 | Exercise capacity.                                                                                                                                                                                                             |
|----------|-----------------------------------------------------------------------------------------------------------------------------------------------------------------------------------------------|---------------------------------------------------------------|-----------------------------------------------------------------------------------------------------------------------------------------------------------------------------------------------------|--------------------------------------------------------------------------------------------------------------------------------------------------------------------------------------------------------------------------------|
| Outcomes | Hospital stay since surgery to discharge: 
 
• Critical care Unity (ICU).
 
• Hospital stay out of ICU.
 
• Total hospital stay.
 
 | Quality of life prior to surgery and six months after surgery | 
 
• Peak expiratory flow.
 
• Inspiratory capacity.
 
• Maximum static inspiratory (MIP).
 
• Maximum static expiratory (MEP).
 
 | 
 
• Aerobic resistance
 
• Lower limb strength.
 
• Hand grip strength
 
• Biceps brachii and quadriceps strength capacity
 
                                |
| Tool     | Accounting of the days according to the data reflected in the medical history.                                                                                                                | EuroQoL-5D questionnaire                                      | 
 
• Sibelmel Datospir Peak-10.
 
• Portex Coach 2 Incentive Spirometer 4000ml.
 
• MicroRPM device (Carefusion)
 
                       | 
 
• 2 minute step test
 
• Short Physical Performance Battery.
 
• Activity logging via Google Fit
 
• Hand dynamometry.
 
• Dynamometer Lafayette
 
 |
| Time     | At hospital discharge                                                                                                                                                                         | Pre-surgery and 6 months after discharge.                     | Pre-surgery, 24h after the surgery, at the hospital discharge                                                                                                                                       | Pre-surgery, 24h after the surgery, at the hospital discharge                                                                                                                                                                  |

1. Hospital stay. Hospital stay will be measured in hours and minutes, so that stays of less than 24 hours can be better accounted for. Three different variables will be recorded:
  - Intensive Care Unit stay: counted from the end of the surgical procedure until transfer to the ward.
  - Ward stay: counted from transfer to ward until discharge from hospital.
  - Hospital stay: counted from the end of the surgical procedure until discharge from hospital.
2. Quality of life. Perception of quality of life will be recorded and assessed both before and six months after surgery. The EuroQOL-5D quality of life questionnaire, valid and reliable for analysing quality of life in this type of patient, will be used. The participant assesses their capacity for self-care, mobility, activities of daily living, the presence of pain or anxiety/depression in categorical levels of severity (no problems, some problems or moderate problems and severe problems) and their perception of health using a visual analogue scale. (34). As there are no published data on the inter-examiner reliability of this tool (35) a single nurse will be responsible for collecting these values.
3. Respiratory values. Respiratory values shall be collected on three different occasions: before surgery, immediately after surgery and on the day of hospital discharge. These tests shall be repeated until three acceptable measurements are obtained (difference <10%), with a one-minute rest between them, and the highest value shall be recorded (36,37). Three measurements shall be made of:

- **Inspiratory capacity:** This is defined as the volume of air that can be inspired from the resting inspiratory position. With the patient in a seated position, the Portex® Coach 2® 4000 ml incentive spirometer will be used to measure inspiratory capacity and the value of the variable will be expressed in millilitres. The patient will be instructed to take a deep, unforced inspiration, trying not to exceed the flow mark (38).
  - **Peak expiratory flow:** This is defined as the maximum flow a person is able to exhale during a brief maximal expiratory effort after a full inspiration. With the patient in a seated position, the Sibelmed® Datospir Peak-10 device will be used to record the peak expiratory flow and the value of the variable will be expressed in litres/second. The patient will be instructed in a maximal forced expiration, preceded by a deep nasal inspiration up to inspiratory reserve volume (39).
  - **Respiratory pressures:** These are used to calculate the strength of the respiratory muscles, both at the diaphragmatic (inspiratory) and abdominal and intercostal (expiratory) levels. Maximum static inspiratory pressures (MIP) and maximum static expiratory pressures (MEP) will be measured in a seated position, using a MicroRPM device (Carefusion, VYAIR MEDICAL, UK). A careful explanation of the test will be given, encouraging the patient to perform a maximal inspiration and inspiration of approximately 2-3 seconds against the resisted device. Predicted values will be estimated using the equation proposed by Heinzmann et al.(40).
4. Exercise capacity. Exercise capacity and endurance will be collected before, 24 hours after surgery and at discharge. The tests used will be:
- **Aerobic capacity:** will be assessed by the 2-minutes Step Test, a valid tool to assess functionality in patients with cardiac pathology after surgery and sensitive to assess perioperative changes. (41)which also has excellent inter-examiner reliability (41). (41). Following the protocol established by Jones and Rikli (42)implemented in 2022 by Chow et al. in revascularised individuals (41)the aim of this test is to count the number of repetitions that each participant is able to perform in two minutes. In case a person needs technical assistance to perform the test, a stable chair will be placed close to him/her to limit the risk of falling. The assessor shall use a manual counter to record the number of steps each person takes by lifting one knee to the middle distance between the patella and the anterior superior iliac spine. (42).
  - **Manual grip strength:** grip strength capacity shall be recorded with manual dynamometry (kg), using a Jamar Plus+® device, which is reliable for measuring changes in patients with cardiac disease, and whose minimum detectable change is 5.2 kg and 5.1 kg for the right and left hand, respectively. (43). With the patient in a seated position, a maximum hand closure is requested for 2-3 seconds, the hand is changed, and the operation is repeated up to 3 times, with a difference of less than 10% between measurements. This tool has inter-examiner reliability (44).

- Analytical strength of the biceps brachii and quadriceps femoris: The strength of the biceps brachii and quadriceps femoris will be measured on the arms and legs with a Dynamometer Lafayette Manual Muscle Tester (Lafayette, IN, USA). (45,46). The measurement technique was described by Bohannon, who verified the excellent intra- and inter-examiner reliability of this tool (47).
- Lower extremity strength: lower extremity strength will be assessed using the Short Physical Performance Battery, a functional test battery that is simple, valid, reliable, sensitive to clinical functional changes and with adequate intra- and inter-examiner reliability (48,49). (48,49). The test consists of three parts:
  - A five-squat test in a standing position, reliable for measuring change, with a minimum detectable change of 3.12 seconds. (43). The time taken to perform the five squats will be categorised according to the following criteria: time less than or equal to 11.19 seconds; between 11.20 and 13.69 seconds; between 13.70 and 16.69 seconds; between 16.70 and 60 seconds; greater than 60 seconds or inability to perform.
  - Static balance, where the participant is asked to adopt three positions during standing: feet together, semi-tandem and tandem. It is quantified if the time they can hold the position is less than or at least 10 seconds.
  - Gait ability, where the patient will be asked to walk in a 4m corridor at a normal pace and the best time in seconds of two attempts will be recorded. Gait ability will be categorised as follows: Unable to perform, time greater than 8.7 seconds; time less than 8.7 seconds, but equal to or greater than 6.21 seconds; time less than 6.20 seconds, but greater than or equal to 4.82 seconds; time less than 4.82 seconds.

